**Methods:**

CaVS patients and clinicians will engage in two cycles of focus groups and usability testing at each site; feedback will be elicited about expectations and experience of SMArTVIEW, in context. The data will be used to refine the SMArTVIEW eHealth delivery program. Upon transfer to the surgical ward (ie, post-intensive care unit [ICU]), 256 CaVS patients will be reassessed postoperatively and randomly allocated via an interactive Web randomization system to the intervention group or usual care. The SMArTVIEW intervention will run from surgical ward day 2 until 8 weeks following surgery. Outcome assessments will occur on postoperative day 30; at week 8; and at 3, 6, 9, and 12 months. The primary outcome is worst postop pain intensity upon movement in the previous 24 hours (Brief Pain Inventory-Short Form), averaged across the previous 14 days. Secondary outcomes include a composite of postoperative complications related to hemodynamic compromise—death, myocardial infarction, and nonfatal stroke— all-cause mortality and surgical site infections, functional status (Medical Outcomes Study Short Form-12), depressive symptoms (Geriatric Depression Scale), health service utilization-related costs (health service utilization data from the Institute for Clinical Evaluative Sciences data repository), and patient-level cost of recovery (Ambulatory Home Care Record). A linear mixed model will be used to assess the effects of the intervention on the primary outcome, with an a priori contrast of weekly average worst pain intensity upon movement to evaluate the primary endpoint of pain at 8 weeks postoperation. We will also examine the incremental cost of the intervention compared to usual care using a regression model to estimate the difference in expected health care costs between groups.

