### Phase 2: Randomized Controlled Trial

#### Methods

##### Trial Design

Research questions to be addressed in a two-group, parallel-arm RCT (see Figure 3) include effectiveness of the intervention to (1) improve postop pain at 30 days (primary outcome) and (2) composite of major postop complications related to hemodynamic compromise, HQRL, depressive symptoms, health service utilization costs, and patient-level cost of recovery (secondary outcomes).

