##### Outcome Measures

###### Primary Outcome

The primary outcome is *worst* postop pain intensity upon movement in the previous 24 hours—at 30 days after randomization—averaged across the previous 14 days. This will be assessed using the Brief Pain Inventory-Short Form (BPI-SF), which has well-established reliability and validity in surgical groups, including CaVS [15,106,107]. Common to studies with postop pain as a primary outcome [15,106,107], patients will report *worst* pain-intensity rating both upon rest and movement in the past 24 hours. The primary outcome of worst pain *upon movement* is a more reliable indicator of suboptimal pain management and pain-related interference with recovery-related activities than worst pain *upon rest* [15,106,107].

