##### Follow-Up

The SVN will collect outcome data for intervention and control groups following random allocation through discharge. Once in the community, patients in both groups will record their BPI-SF pain scores daily for 8 weeks using the tablet-based solutions. Data on 30-day event rates (ie, major postop complications) and hospital readmissions for both groups will be collected by a blinded RA via telephone interview at 30 days postoperation. At 3, 6, 9, and 12 months, additional telephone interviews conducted by the RA will assess (1) functional status, (2) depressive symptoms, (3) CPSP, and (4) patient-level cost of recovery (ie, AHCR).

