### Data Analyses

#### Primary Analyses

Table 3 summarizes all data analyses. Using the intent-to-treat principle [128], all patients will be included in the final analysis and according to the group to which they were randomly allocated. Descriptive statistics will be used to describe sample characteristics using measures of central tendency and dispersion for continuous factors, and frequencies and proportions for categorical factors. A two-sided significance level of .05 will be used for all inferential analyses. Statistical methods used will depend on the type and distribution of data for the outcome variable under study. If outcome data meet requirements for parametric statistics, a linear mixed model [129] will be used to assess the effects of the intervention on the primary outcome. An a priori contrast of the weekly average worst score for the BPI-SF numeric rating scale *upon movement* (previous 24 hours) will be used to evaluate the primary endpoint of acute postop pain at 30 days postrandomization.

Linear mixed models, using an autoregressive [130] covariance structure—allowing for correlations between measurements to decline as they are further apart in time—will be used to evaluate within-patient variation in patient-reported outcomes over 12 months of follow-up. Linear mixed models are a flexible and powerful approach to the analysis of data with a complex variance structure, such as correlated data [129-131]. Unlike traditional repeated-measures designs, these models do not require complete data on each patient and have increased statistical power [132]. Nonlinear mixed models will be used in the following cases: (1) if continuous data violate assumptions of normality [132] and (2) for categorical secondary outcomes (eg, adverse event). Chi-square tests of association will be used to assess the association between categorical secondary outcomes identified in the administrative data and intervention. Given that the data is derived from an RCT, complex modeling for these outcomes will not be performed, as potential confounders are considered to be adjusted for in the design. Finally, we will examine patterns of missing data and determine demographic and/or clinical characteristics that are related to missing data at each time point, and the potential impact on the primary findings.

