**Primary outcome**				
	8-week worst postop pain intensity *upon movement* score in the past 24 hours	Intervention > control	Measured by Brief Pain Inventory-Short Form (BPI-SF^a^)	Linear mixed model or nonlinear mixed models (if assumptions of normality are violated)

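### The primary endpoint is 30 days after randomization in the Methods text but 8 weeks in the Abstract and Table 3, with two averaging windows, so no single primary test is fixed

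*Protocol article*

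**What the plan says.** The protocol article describes the primary outcome or its test in five places.

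- **Trial Design (Phase 2)** gives pain at 30 days as the primary outcome, with no origin or averaging window.
- **Outcome Measures, Primary Outcome** specifies worst "pain intensity upon movement in the previous 24 hours—at 30 days after randomization—averaged across the previous 14 days".
- **Data Analyses, Primary Analyses** plans "An a priori contrast of the weekly average worst score for the BPI-SF numeric rating scale" on movement, which "will be used to evaluate the primary endpoint of acute postop pain at 30 days postrandomization".
- **Abstract, Methods** first describes the outcome as a mean over the preceding 14 days without a time point. It then plans a contrast of "weekly average worst pain intensity upon movement to evaluate the primary endpoint of pain at 8 weeks postoperation".
- **Table 3**, primary outcome row, reads "8-week worst postop pain intensity" on movement in the past 24 hours, with no averaging window.

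Under Follow-Up, "patients in both groups will record their BPI-SF pain scores daily for 8 weeks using the tablet-based solutions", so the data would support either time point.

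**The concern.** A confirmatory trial needs one primary quantity: one variable, one time, one origin and one summary. Here the time differs by almost four weeks between places, the summary differs between the definition and its own test, and the origin moves between randomization and operation. An analyst who follows the Primary Outcome section and one who follows Table 3 would run different tests on non-overlapping data, and each could say that the protocol was followed.

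Two things are at stake. The first is error control: the nominal 5% applies to one prespecified test, not to whichever of several proves favourable. The second is meaning: at 30 days patients are still receiving parts of the intervention, whereas the Abstract has the intervention ending at 8 weeks after surgery. The two endpoints therefore answer different questions.

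**Working it through.** **1. The statements side by side**

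| Place | Time point | Origin | Averaging |
|---|---|---|---|
| Abstract, outcome sentence | not given | not given | 14 days |
| Abstract, analysis sentence | 8 weeks | operation | weekly |
| Trial Design | 30 days | not given | not given |
| Primary Outcome | 30 days | randomization | 14 days |
| Primary Analyses | 30 days | randomization | weekly |
| Table 3, primary row | 8 weeks | not given | none (past 24 hours) |

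The time conflict is not only between Abstract and body. Primary Analyses refers the reader to Table 3 as the summary of every analysis, then sets 30 days in the same paragraph, while Table 3 says 8 weeks. The window conflict occurs within the Methods text and again within the Abstract.

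**2. The candidate quantities**

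Two time points and two windows give 2 × 2 = 4 candidates. Counting days from the chosen origin:

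- 30 days, 14-day mean: days 17-30 (30 − 14 + 1 = 17)
- 30 days, weekly mean: days 24-30
- 8 weeks (day 56), 14-day mean: days 43-56
- 8 weeks, weekly mean: days 50-56

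From a common origin, the 30-day and 8-week candidates share no days.

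**3. Does the sample size settle it?**

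Inputs from Sample Size: SD 20, difference 10, two-sided alpha 0.05, power 80%.

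- Normal formula: n per group = 2 × (1.96 + 0.842)² × 20² / 10² = 62.8, so 63. The two-sample t-test gives 63.8, so 64 per group and 128 in total, as stated.
- Dropout: 64 / 0.90 = 71.1, so 72 per group and 144 in total, as stated.
- Combined sample: 256 / 1.5 / 2 = 85.3 effective per group. The detectable difference is 2.80 × 20 × √(2 / 85.3) = 8.58 (8.63 by t-test), against 8.6 stated.

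All three figures reproduce, but none depends on a time point or window. They cannot show which endpoint was powered.

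The SD does depend on the window. Suppose 20 is the SD of a single daily score and the day-to-day correlation is 0.7; both are assumptions. With exchangeable correlation, SD of an m-day mean = 20 × √[(1 + (m − 1) × 0.7) / m], which is 17.2 for 7 days and 17.0 for 14 days. With first-order autoregressive correlation the values are 14.4 and 11.4.

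**4. Type I error if the better result could be called primary**

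For independent tests at 0.05 each: 1 − 0.95² = 9.75% with two candidates and 1 − 0.95⁴ = 18.5% with four. For correlated tests, the simulated probability that at least one |Z| exceeds 1.96 is:

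| Correlation (assumed) | Two candidates | Four candidates |
|---|---|---|
| 0.4 | 9.3% | – |
| 0.5 | 9.1% | 15.6% |
| 0.6 | 8.8% | – |
| 0.7 | 8.3% | 13.1% |
| 0.8 | 7.8% | 11.4% |
| 0.9 | 7.0% | 9.4% |

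The document gives no correlations. The 7-day and 14-day means at one time point share data, so the high-correlation rows are the more realistic ones for four candidates.

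**5. Where day 30 falls in the intervention**

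Assume discharge 4-7 days after randomization. Day 30 is then (30 − 4)/7 = 3.7 to (30 − 7)/7 = 3.3 weeks after discharge. With one Restore module a week from the week of discharge, about 4 of 7 have been released. The daily nurse check-ins in Table 2 last 30 days after discharge, so 23-26 of those days have passed.

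**The case against.** The strongest reply is that the intended endpoint is fairly clear. All three body-text statements of the time point say 30 days, and the two that give an origin say randomization. Feasibility also has equipment returned at 30-day follow-up. On this reading, the 8-week wording is unreconciled text in the Abstract and one table row. That makes 30 days the likelier intent, but it does not remove the contradiction: Table 3 is the designated summary of the analyses, and nothing says which statement prevails.

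Second, the windows may be compatible, because days 17-30 are two 7-day weeks and the mean of two weekly means equals the 14-day mean when data are complete. The text does not say this. It also works only if weeks are counted back from day 30. Counted forward from randomization, the nearest weeks are days 15-21, 22-28 and 29-35, and no pair of them gives days 17-30. This conflict is nonetheless more easily repaired than the one over time.

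Third, the origin matters little in practice. Randomization is at transfer to the ward, and the Introduction puts most patients in the ICU for 12-24 hours, so the shift is usually about a day. That stands; the origin is a minor mismatch.

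Fourth, the description of week 8 as the end of the programme is not uniform. The Self-Management Training section ends Restore at week 6 after operation, Table 2 at 7 weeks after discharge, and the Abstract ends the intervention at 8 weeks after surgery. Day 30 is about halfway for Restore only and late for the check-ins. Both points stand as qualifications.

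Finally, the error rates require a choice made after seeing results, with no other document fixing the endpoint. They illustrate a risk. They are not an operating characteristic of the plan.

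**Conclusion.** The concern holds. As written, the protocol article supports two incompatible primary tests, at 30 days and at 8 weeks, and leaves the averaging window open at either time. The contradiction is in current text and needs no assumption to establish.

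Its size does rest on assumptions: a type I error of about 7.8-9.3% instead of 5% if either time point could be claimed, for correlations of 0.8 to 0.4, and somewhat more if the window were also chosen freely. The stated sample sizes are arithmetically sound but tied to no particular endpoint. The required number for the chosen endpoint cannot be recomputed, because no SD is given for it. This should be corrected before randomization begins.

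**What to change.** Choose one time point, one origin and one averaging window, and use the same wording in the Abstract, Trial Design, Primary Outcome, Primary Analyses and Table 3.

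- **Default:** keep the Primary Outcome definition, that is, the mean of daily worst movement pain over days 17-30 after randomization. Write the mixed-model contrast so that it estimates exactly this quantity, either from the 14-day mean itself or from two stated 7-day means covering those days. Name the 8-week score as a secondary outcome; ranking it first would be sensible.
- **If 8 weeks is preferred:** change all three Methods statements, and reconcile the equipment return at 30 days in Feasibility with the eight weeks of daily tablet entries in Follow-Up. If the returned equipment includes the tablets, the stated collection method does not reach week 8.
- **In either case:** say in Sample Size which endpoint the SD of 20 refers to, and whether it is the SD of a single daily score or of the average.

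The default costs only wording, in this document and in any registry entry or analysis plan that repeats the endpoint. The 8-week option may also need more equipment time. If recruitment has already started, make the change by dated amendment before anyone sees outcome data by group, because a later change would be open to the charge of outcome switching.

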###### Secondary Outcomes

####### Postoperative Complications Related to Hemodynamic Compromise

We will capture a composite of complications related to hemodynamic compromise up to 30 days postrandomization, including death, myocardial infarction, and nonfatal stroke. The number of events for the overall composite, as well as number of events per component within the composite, will be reported.

####### All-Cause Mortality and Other Postoperative Complications

All-cause mortality will be captured up to 1 year postrandomization. We will also monitor for new-onset atrial fibrillation and SSI up to 30 days postrandomization.

####### Functional Status

The Short-Form 12 version 2 (SF-12v2) is an established, reliable, and valid tool [108,109] to measure functional status [108,109]. The SF-12v2 provides both physical component summary and mental component summary scores [9,11,46,109].

####### Depressive Symptoms

The five-question version of the Geriatric Depression Scale (GDS-5) will be used to measure depressive symptoms. This tool is a well-validated instrument in the assessment of depression in hospitalized older adults, with high levels of sensitivity and specificity [110,111].

####### Chronic Postsurgical Pain

Development of CPSP is defined [112] as (1) pain that developed after the surgical procedure, (2) being different from pain experienced before surgery, and (3) being present for at least 3 months. Patient responses in the affirmative to each of these questions indicate patients have developed CPSP. For patients who have developed CPSP, pain intensity and related interference with usual daily activities will be measured via the BPI-SF [106,107].

####### Heath Service Utilization-Related Cost

Data on hospital readmission and health care utilization and costs of health service utilization data from the Canadian arm of the trial will be linked with the health administrative Institute for Clinical Evaluative Sciences data repository. Administrative databases used to describe the health service utilization include (1) Registered Persons Database—demographics and vital statistics of all legal residents of Ontario, (2) Discharge Abstract Database—records of inpatient hospitalizations—from the Canadian Institute for Health Information (CIHI), (4) Ontario Health Insurance Plan Database—physician billing claims, and (5) the National Ambulatory Care Reporting System—information on emergency department visits—from CIHI. In addition, to capture data on times spent on the portal by health providers (eg, pharmacists and nurses), costs of health providers’ time will be captured in the system reporting. Costs of health providers’ time on the portal will be calculated by multiplying the time with unit costs from standard costing sources in Ontario.

####### Patient-Level Cost of Recovery

The Ambulatory and Home Care Record (AHCR) [11,113-117] will be used to comprehensively measure patient-level cost of illness from a societal perspective (Canada and the United Kingdom). This approach gives equal consideration to health system costs and costs borne by patients and unpaid caregivers (eg, family members and friends). AHCR items can be categorized as publicly financed (eg, public sector paid resources) or privately financed care (eg, all out-of-pocket and third-party insurance payments, and time costs incurred by caregiver). Face validity and reliability of the AHCR is well-established in multiple groups, including CaVS patients [11,113-117].

##### Baseline Measures to Inform Subgroup Analyses

Aside from baseline clinical and demographic information, gender-based pain expectations [118] will be assessed to inform subgroup analyses as evidence suggests that gender-based pain expectations may lead to differences in the experience of pain and related response to interventions [118]. These expectations will be captured using the Gender Role Expectations of Pain (GREP) tool, which captures stereotypic attributions regarding pain endurance, pain sensitivity, and willingness to report pain. The GREP tool has been used in multiple pain investigations [118-123] with acceptable test-retest and internal consistency reliability [118].

Baseline digital literacy will also be assessed using an adapted version of the informational and instrumental support domains of the Patient-Reported Outcomes Measurement Information System (PROMIS) measures. This approach, previously pilot-tested with cardiovascular patients [124], employs five items to examine current level of engagement with mobile and digital technologies.

##### Follow-Up

The SVN will collect outcome data for intervention and control groups following random allocation through discharge. Once in the community, patients in both groups will record their BPI-SF pain scores daily for 8 weeks using the tablet-based solutions. Data on 30-day event rates (ie, major postop complications) and hospital readmissions for both groups will be collected by a blinded RA via telephone interview at 30 days postoperation. At 3, 6, 9, and 12 months, additional telephone interviews conducted by the RA will assess (1) functional status, (2) depressive symptoms, (3) CPSP, and (4) patient-level cost of recovery (ie, AHCR).

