#### Undetected Hemodynamic Compromise

CaVS are among the highest-risk surgeries and are associated with substantial postop morbidity and mortality. Following an immediate postop period of intensive care unit (ICU) hemodynamic surveillance, vital signs monitoring after ICU discharge is lacking. Most patients on surgical wards will have vital signs evaluated once per 4-12 hours [54,55]. Such limited in-hospital monitoring—followed by no daily monitoring at home—is significantly associated with poor clinical outcomes. For example, in a study from the Cleveland Clinic [56], nurses blinded to continuous pulse oximetry for monitoring peripheral oxygen saturation (SpO_2_) assessed their postop patients (n=594) according to normal practice and detected a 5% incidence of hypoxemia (SpO_2_< 90%). Blindly captured study oximetry, however, detected that 37% of patients had one or more continuous episodes of hypoxemia for ≥1 hour, and that 10% of patients had at least one continuous episode (≥1 hour) of hypoxemia where SpO_2_ was <85% [56]. Given that hypoxemia for >5 minutes is associated with increased risk of myocardial ischemia, suboptimal monitoring on surgical wards elevates risks for patients. Studies have also demonstrated that continuous electrocardiographic ST segment monitoring after surgery can identify asymptomatic ischemia that is independently associated with myocardial infarction [57-59]. A study of postop ST segment depression followed 151 consecutive patients undergoing major vascular surgery and assessed for postop myocardial ischemia [57]. Approximately 85% of patients who suffered postop cardiac events had preceding long-duration ST segment depressions [57]. These data suggest that remote, continuous, noninvasive ST segment monitoring systems can identify impending cardiac events much sooner than the usual practice of checking vital signs manually every 4-12 hours. The same is true for cardiac postop arrhythmias. The incidence of atrial fibrillation, in particular, is 20-40% after cardiac surgery, with even higher rates (30-50%) after valvular surgery [60-62]. While most patients spend the first 12-24 hours after surgery in the ICU, 70% of postop atrial fibrillation occurs over the first 4 days following surgery, suggesting that many occurrences will be missed on surgical wards [63]. This common scenario is risk elevating, given that atrial fibrillation imposes a three-fold increase in hypotension and stroke [64,65].

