**Stage 1: In hospital**		
	**IntelliVue Guardian setup** **(ward day 1)**	
		Upon transfer to the ward, the IntelliVue Guardian early warning system is established by the SVN^b^ on duty, who connects patient to peripheral, cableless devices; establishes baseline/normal vital signs with spot check monitor; activates IntelliVue Guardian; and performs system checks every shift.
		The SVN will receive alerts via mobile device; alerts will be set according to surgeon-sanctioned vital signs parameters programmed into IntelliVue Guardian, which allow for tailoring of profiles for day or night, as well as pre-existing comorbid conditions (eg, atrial fibrillation).
		Upon alerts, SVN assessment, intervention, and escalation of care will be according to usual hospital protocols.

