### Controls for Bias

To limit sampling bias, a recruitment schedule randomly generated to ensure representation from each surgical group will be used. Contamination should not exist between groups as we will control who interacts with the SVN and intervention features. Those allocated to the intervention group will be asked not to share their tablets or demonstrate application features to any peers assigned to the control group. To evaluate cointervention, we will track participant receipt of any monitoring or recovery support-related interventions, outside of expected usual care up to 8 weeks postoperation. RAs responsible for outcome data collection will be separated from randomization procedures, will have no permitted access to IWRS, will not be involved in intervention delivery, and will be blinded to group allocation. An event adjudication committee responsible for adjudication of all clinical outcome data will be blinded to randomized allocation. The team has extensive experience with assiduous follow-up procedures to minimize losses to follow-up.

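### The unblinded intervention nurse collects in-hospital outcomes in both arms, and ward atrial fibrillation appears to be sought more intensively in the intervention arm, so atrial fibrillation counts cannot be compared between arms.

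*Protocol article*

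**What the plan says.** **Who collects.** Follow-Up states: "The SVN will collect outcome data for intervention and control groups following random allocation through discharge". Table 2 gives the same nurse the delivery of the intervention. On ward day 1, "the IntelliVue Guardian early warning system is established by the SVN", and the nurse then receives the alerts, leads the orientation and pain education, and makes the daily home check-ins.

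**Stated safeguards.** Controls for Bias says that the RAs who collect outcome data "will not be involved in intervention delivery, and will be blinded to group allocation". It also says: "Contamination should not exist between groups as we will control who interacts with the SVN and intervention features". For the month after surgery, Follow-Up adds: "Data on 30-day event rates (ie, major postop complications) and hospital readmissions for both groups will be collected by a blinded RA via telephone interview". Controls for Bias further provides: "An event adjudication committee responsible for adjudication of all clinical outcome data will be blinded to randomized allocation".

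**How events are found.** Under Stage 1, Monitoring, intervention patients have continuous 8-lead ECG and continuous oxygen saturation on the ward, with a blood pressure cuff and a respiration sensor. Stage 2 adds home vital signs, wound surveys and 30 days of daily video contact. For surgical wards in general, Undetected Hemodynamic Compromise describes vital signs every 4-12 hours. It notes that 70% of postoperative AF arises in the first 4 days, "suggesting that many occurrences will be missed on surgical wards".

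**The outcomes.** Secondary Outcomes defines a 30-day composite of death, MI and nonfatal stroke, and then states: "We will also monitor for new-onset atrial fibrillation and SSI up to 30 days postrandomization".

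**The concern.** There are two separate problems.

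First, between randomization and discharge the outcome collector is someone who knows allocation and delivers the intervention. The separation promised for RAs does not reach this period. The contamination argument rests on controlling who meets the SVN, yet Follow-Up brings the SVN to control patients.

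Second, the intervention is itself a detection device. The protocol's rationale is that ordinary ward checks miss arrhythmias that continuous monitoring would find. When AF is then counted as an outcome, the arm with the better detector will tend to show more of it, whatever the true risk. The same argument reaches MI, because the protocol says that continuous ST monitoring finds asymptomatic ischemia, and SSI, because only the intervention arm is described as having wound surveys. At stake are a spurious excess in the intervention arm, or a real reduction that is hidden.

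**Working it through.** **1. Setting the sections side by side**

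| Period | Collector | Blinded? | Outside delivery? |
|---|---|---|---|
| Randomization to discharge | SVN, both arms | No (runs the intervention) | No |
| Home, to 8 weeks (pain) | Patient, by tablet, both arms | Self-report | Not applicable |
| 30-day events and readmissions | RA, by telephone | Yes, as stated | Yes, as stated |
| 3-12 months | RA, by telephone | Yes, as stated | Yes, as stated |

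The first row is the gap.

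**2. Size of the detection effect for AF**

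The plan gives no detection figure to reproduce. The one plan figure used is 256 patients with complete data across two sites (Sample Size), that is 128 per arm. It rests on 64 per group per site, which reproduces: a difference of 10 points, SD 20 and two-sided 0.05 give 80.1% power with 64 per group (noncentral t).

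Assumptions, none of them in the document:
- true AF risk p is equal in both arms;
- telemetry finds all ward AF;
- control care finds a fraction s of it, with s from 0.6 to 0.9.

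Observed risks are p and s·p, so the apparent risk ratio is p/(s·p) = 1/s, whatever the value of p. If the intervention truly cut AF by 30%, the observed ratio would be 0.7/s.

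| s | No true effect: 1/s | True 30% reduction: 0.7/s |
|---|---|---|
| 0.9 | 1.11 | 0.78 |
| 0.8 | 1.25 | 0.875 |
| 0.7 | 1.43 | 1.00 |
| 0.6 | 1.67 | 1.17 |

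At s = 0.7 a true 30% reduction vanishes.

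**3. Chance of a false significant excess**

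This uses a two-sided 0.05 normal-approximation test of two proportions with 128 per arm. For p = 0.30 and s = 0.7, the observed risks are 0.30 and 0.21, with mean 0.255.
- Standard error under the null: √(2 × 0.255 × 0.745 / 128) = 0.0545.
- Standard error under the alternative: √((0.30 × 0.70 + 0.21 × 0.79) / 128) = 0.0542.
- Power: Φ((0.09 − 1.96 × 0.0545) / 0.0542) = Φ(−0.31) ≈ 0.38.

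Over p = 0.20 to 0.40, the chance is 6-10% at s = 0.9, 13-26% at s = 0.8 and 25-53% at s = 0.7.

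These probabilities are illustrative. The 20-40% range is the protocol's figure for cardiac surgery, while Feasibility targets 14 cardiac and 16 vascular patients per site and wave. Some AF will also arise in intensive care, before randomization. A lower p reduces the chance of a false significant result but leaves 1/s unchanged.

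**4. Which outcomes are reached**

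- AF: strongly, on the ward. The home kit lists no ECG, so AF arising after discharge and found equally in both arms would pull the 30-day ratio toward 1.
- MI: plausibly, through ECG-detected or silent events.
- SSI: plausibly, through the wound surveys and daily contact.
- Stroke: weakly, since most strokes that count are clinically evident.
- Death: negligibly.

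**The case against.** The strongest reply is that the protocol does protect its event data. A blinded RA collects 30-day major complications and readmissions in both arms, and a blinded committee adjudicates all clinical outcomes. A reader might infer that complication rates as a whole are unblinded; the documents do not support that. What these safeguards protect is classification. A patient cannot report on the telephone an AF episode that nobody noticed, and no record of it would reach the committee.

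Four further points stand and limit the concern.

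- The two sections do not flatly contradict each other. Controls for Bias claims blinding for RAs, not for the SVN, and says that SVN contact will be controlled, not that controls will have none. The SVN also assesses every consented patient for confusion before randomization.
- A reader might infer that controls receive pain-management teaching from the SVN. Nothing says so: Follow-Up gives the SVN only data collection in that arm. The contact is an opportunity for contamination, not a documented instance of it.
- AF is an outcome to be monitored, but it is absent from the composite and from Table 3. No AF benefit is hypothesized, so it would be wrong to say that detection bias reverses one. MI and SSI are in Table 3.
- The absence of continuous monitoring in controls is inferred from the description of usual care; the article does not describe control-arm monitoring directly.

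**Conclusion.** The point holds in a limited form. In-hospital outcomes in both arms are collected by an unblinded nurse who delivers the intervention, which does not fit the separation described for the other outcome collectors. AF counts are not comparable between arms on the protocol's own reasoning, and the article states no common means of detection. If usual care finds 60-90% of the ward AF that telemetry finds, equal true risk would appear as a risk ratio of 1.67-1.11 against the intervention. That range rests wholly on the assumed s, on complete detection by telemetry, and on controls not being continuously monitored.

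A reader might carry this over to the primary outcome. The detection problem does not reach it: after discharge, patients in both arms record pain themselves, daily, by tablet. The matter therefore concerns secondary outcomes. It should be corrected, but it does not undermine the main comparison.

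**What to change.** 1. Reassign in-hospital outcome collection in both arms to the existing RAs who take no part in delivery, using chart abstraction where possible to protect blinding. Remove the SVN's outcome role for controls, and reconcile Follow-Up with Controls for Bias.
2. For the between-arm comparison, count AF, MI and SSI only from sources and time points common to both arms.
3. Report detections triggered by the ward monitors or the home system (eTrAC) separately, as a process measure.
4. State that AF will not be interpreted as an efficacy or harm comparison.

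Two simpler rules would not do. Counting only events that the ward team acted on keeps the bias, because monitor alerts themselves prompt assessment and escalation (Table 2). Stripping monitor output from adjudication packets could remove the ECG evidence in one arm only and bias the result the other way.

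The cost is a task moved to staff already in the trial and fewer counted AF events. RA blinding on the ward may remain imperfect, since devices and chart entries can reveal the arm.
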